### Participant and staff experience

During both blocks, patient/carer and staff experiences will be explored through surveys. A short patient and carer survey will explore the patient/carer’s experience and whether they felt sufficient stimulation was offered to assist early rehabilitation and recovery during the acute stay. Staff surveys will be handed out to 25 nursing and therapy staff members of the unit. These surveys will explore their perceptions of innovation, patient care, team relationships, work satisfaction, and workload during each block. In addition, after block 2, up to ten semi-structured interviews with nursing and therapy staff will be conducted until saturation of data is reached. These interviews will focus on staff experience during the EE intervention period only. Questions will aim to explore perceived barriers in implementing an EE and what staff will need to be able to sustain the EE in the future. Thematic content analysis will be performed on all qualitative data. Figure 1 shows a flow chart of the pilot study.

**Fig. 1 Fig1:**
[figure not shown]
Flowchart of study. *NIHSS* National Institutes of Health Stroke Scale, *mRS* modified Rankin Scale, *MSAS* Mobility Scale for Acute Stroke, *MBI* Modified Barthel Index, *HADS* Hospital Anxiety and Depression Scale, *EE* enriched environment, *AE* adverse events, *SAE* serious adverse events

### Sample size

We performed a sample size calculation to ensure that this pilot study has sufficient power to determine significant positive effect on our primary outcome measure—total activity levels in stroke survivors. Estimates were based on data from a recent study of the effect of an EE on activity levels conducted during inpatient stroke rehabilitation [15]. This study reported a mean increase in the proportion of observations with 'any activity' in the EE group of 13 % (SD 14) and the control (no EE) group of 2 % (SD 16.5), equivalent to an effect size of 0.719. We performed a one-sided, between-groups test as this past research has shown an enriched environment to increase activity levels in stroke survivors [15]. Based on a rounded effect size of 0.7, we calculated that we would need to recruit 26 participants per group to detect one standard deviation difference between EE and non-EE groups for any activity with an alpha level of 0.05 and a power of 0.8. Allowing for a conservative dropout rate of 12 %, we will aim to recruit 30 participants per group.

### Statistical analysis

Baseline characteristics of participants will be described using means and standard deviations for continuous variables and counts and percentages for categorical variables. To address the primary outcome (change in activity levels for 'any activity'), we will compare the proportion of activity between usual care and EE intervention group. We will assume that at each observation, the participant remains engaged in that activity for the entire 10-min interval; this will allow us to calculate the proportion of time each group is engaged in any activity. Subsequently, we will explore for differences in each activity domain and subcategories within domains. Consistent with previous research in the field [15], unobserved and missing data will be excluded from the analysis for the primary outcome of change in activity level. Total number of observations per participant will be summed and used to calculate the proportion of observations each participant is observed to be engaged in any activity (and physical, social, and cognitive activity and other fields included in the data collection sheet). The difference in activity levels between groups will be determined using one-way ANCOVA with group as independent variable, activity levels as the dependent variable, and adjusting for covariates age (years), stroke severity (NIHSS), and premorbid function (mRS). To determine differences in secondary outcome measures between groups, one-way repeated-measures ANCOVA will be performed for variables separately, adjusting for age (years), stroke severity (NIHSS), and premorbid function (mRS). We will adjust for the above covariates as these covariates impact on activity levels, functional outcomes, and mood in stroke survivors [27–29].

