**Methods/design:**

We will perform a prospective non-randomized before-after intervention study. The primary aim is to determine if an EE can increase physical, social, and cognitive activity levels of people with stroke in an ASU compared to usual care. Secondary aims are to determine if fewer secondary complications and improved functional outcomes occur within an EE. We will recruit 30 people with stroke to the usual care block and subsequently 30 to the EE block. Participants will be recruited within 24–72 h after onset of stroke, and each block is estimated to last for 12 weeks. In the usual care block current management and rehabilitation within an ASU will occur. In the EE block, the ASU environment will be adapted to promote greater physical, social, and cognitive activity. Three months after the EE block, another 30 participants will be recruited to determine sustainability of this intervention. The primary outcome is change in activity levels measured using behavioral mapping over 12 h (7.30 am to 7.30 pm) across two weekdays and one weekend day within the first 10 days of admission. Secondary outcomes include functional outcome measures, adverse and serious adverse events, stroke survivor, and clinical staff experience.

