### Baseline measures

Baseline measures will include demographics; previous mRS and living arrangements; stroke details such as date, estimated time of onset, lesion location and type, Oxford Stroke Classification, and National Institute of Health Stroke Scale (NIHSS). Stroke severity will be classified according to NIHSS [21] on admission (day 1 if thrombolyzed): mild (<8), moderate (8–16), and severe (>16).

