### Secondary outcomes

Secondary measures to be collected include functional outcomes, adverse and serious adverse events, and mood. Functional outcomes will be assessed with the mRS, modified Barthel index (MBI), 10-m walk test, and Mobility Scale for Acute Stroke patients (MSAS). Mood will be assessed with the Hospital Anxiety and Depression Scale (HADS), and nutritional status will be determined through weight and the Subjective Global Assessment (SGA) to assess for malnutrition. Serious adverse events (SAE) are defined as an adverse event that led to death and/or led to serious deterioration in health of a patient, whereas adverse events (AE) are defined as any untoward or unfavorable medical occurrence in a patient. Complications recorded include falls, pneumonia, pressure areas, cardiac problems, seizures, reduced Glasgow Coma Scale, stroke, transient ischemic attack, urinary tract infection, depression, constipation, malnutrition, delirium, and “other” including shoulder pain, deep venous thrombosis, and urinary retention [24, 25].

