### Data collection time points

An investigator will conduct the initial assessment on entry to the study. Blinded assessors will perform discharge assessments immediately prior to discharge from the ASU or when a decision for palliative intent is made. Blinded assessors will also undertake follow-up phone calls at 3 months post-stroke to determine mRS, living arrangement, Health State Score [26], and if any SAEs have occurred after discharge. Three months after the EE block, another period of behavioral mapping will occur to determine whether activity levels have been sustained in the ASU. We aim to recruit 30 participants using the same eligibility criteria and complete behavioral mapping on a single, randomly chosen day from 7.30 am till 7.30 pm.

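### Repeated-measures ANCOVA is the only between-group method stated for secondary outcomes, but it does not fit complications, adverse events, serious adverse events or the Health State Score

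*Protocol article*

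**What the plan says.** The method sentence in the Statistical analysis section covers secondary outcomes as a class and makes no exception: "one-way repeated-measures ANCOVA will be performed for variables separately". The covariates are age, NIHSS and premorbid mRS. No other between-group method for secondary outcomes appears in the article.

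The Secondary outcomes section puts events in that class: "Secondary measures to be collected include functional outcomes, adverse and serious adverse events, and mood". It then lists more than a dozen kinds of complication, beginning "Complications recorded include falls, pneumonia, pressure areas, cardiac problems, seizures".

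The abstract turns complications into a between-group question: "Secondary aims are to determine if fewer secondary complications and improved functional outcomes occur within an EE". The Background repeats this as a hypothesis. The Fidelity of the intervention section makes safety of the EE one part of its main measure of successful implementation.

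On timing, the Data collection time points section describes "follow-up phone calls at 3 months post-stroke to determine mRS, living arrangement, Health State Score [26], and if any SAEs have occurred after discharge". The Baseline measures section shows that two of these items also have an earlier value: "Baseline measures will include demographics; previous mRS and living arrangements".

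**The concern.** Repeated-measures ANCOVA needs one roughly continuous variable, measured on the same participant on at least two occasions. Complications and serious adverse events are yes/no or count outcomes that accrue over a period, so the model has no series of values to work on. The Health State Score, as described, has a single occasion.

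At stake are one of the two secondary aims in the abstract and the safety comparison that forms part of the definition of success. An analyst who follows the sentence must decide, possibly with the data in view, how to code time for an event and which model term to report. In an unrandomized before-after comparison with 30 participants per block, that choice should not be left open.

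**Working it through.** **The plan's own figure.** The article gives no figure for complications. Its only calculation is the sample size for the primary outcome, and this reproduces: d = (13 − 2)/√((14² + 16.5²)/2) = 0.719. With d = 0.7, one-sided alpha 0.05 and power 0.8, n = 26 per group, and 26/0.88 = 29.5, so 30. Nothing below changes it.

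**Which outcomes fit the stated model, by what the text says of timing.**
- *MBI, 10-m walk test, MSAS, HADS, weight:* scales or measurements for which entry and discharge assessments are described. The sentence suits them in form.
- *mRS:* premorbid value at baseline, also a functional outcome, and again at 3 months. It is repeated.
- *Living arrangement:* baseline and 3 months. It is repeated, but it is a category.
- *SGA:* a category; its timing is not given in the text, and Figure 1 is not available here.
- *Health State Score:* mentioned only at the 3-month call.
- *Complications, adverse events, serious adverse events:* events over the stay; serious events are also asked about for the time after discharge.

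**What happens if events are forced in.** The documents give no complication risks, so these inputs are assumptions: 15 of 30 with a complication under usual care, 9 of 30 under EE, and none at entry.

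Single-time comparison:
- Risk difference = 15/30 − 9/30 = 0.20.
- Sample variances: (15 × 15/30)/29 = 0.2586 and (9 × 21/30)/29 = 0.2172.
- SE = √((0.2586 + 0.2172)/30) = 0.1259; t = 0.20/0.1259 = 1.588 on 58 df; p = 0.118.

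The group main effect compares each participant's average over the time points. With y = 1 for an event and 0 otherwise:

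| Time coding | Participant average | Group main effect | p |
|---|---|---|---|
| two times (0, y) | y/2 | 0.20/2 = 0.100 | 0.118 |
| three times, carried forward (0, y, y) | 2y/3 | 0.20 × 2/3 = 0.133 | 0.118 |
| three times, counted once (0, y, 0) | y/3 | 0.20/3 = 0.067 | 0.118 |

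The group-by-time contrast from entry to the next occasion is y − 0 = y. It returns the full 0.20 in every layout, also with p = 0.118. The p-value does not move because each quantity is a constant multiple of y, so the effect and its SE scale together.

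Covariate adjustment does not alter this. In 1,500 simulated data sets with two times and age, NIHSS and premorbid mRS in the model, the mean effect was −0.199 for the single-time analysis and −0.100 for the group main effect. Both rejected in 32.8% of data sets, with identical p-values.

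The reported size therefore runs from one third of the risk difference to all of it, according to choices that the article does not state.

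**The case against.** The strongest reply is that the sentence was meant for the repeated scales only. The covariates are justified by their influence on activity, function and mood, with no mention of complications, and the tabulation of sparse events in a pilot is often left to a fuller plan. That reading of the intent is plausible, and nothing shows that the investigators would put yes/no events into this model. But the text assigns the method to secondary outcomes without exception and counts events among them. This is a method wrongly fixed, not a detail left out.

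Several stronger readings are tempting, and the documents do not support them:
- *The effect on complications would always be halved.* Half needs exactly two times, zeros at entry and the group main effect. The zeros are themselves insecure, since malnutrition, depression, constipation and pressure areas could be present at entry.
- *The test would reach a different result.* In the layouts above the p-value equals that of a single-time linear ANCOVA.
- *All 3-month outcomes are measured once.* mRS and living arrangement are also recorded at baseline. Only the Health State Score and serious events after discharge are described solely at 3 months.
- *Rare events make the linear model misleading.* At an assumed 3% or 5% risk, a block of 30 has no event with probability 0.97^30 = 0.40 or 0.95^30 = 0.21. In simulation, linear ANCOVA then rejects a true null in about 1.3–1.6% or 2.6–2.8% of runs. At 10% risk it is near nominal (4.6–4.8%). This shows only conservatism at assumed risks. Fisher's exact test is more conservative still (0.03%, 0.2% and 1.0% at 3%, 5% and 10%). It is no argument for an exact test, and the aim concerns complications as a whole.
- *mRS must be analyzed by ordinal regression.* That is a preference and no part of this point.

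**Conclusion.** The point holds in limited form. The one method stated for secondary outcomes does not fit complications, adverse events, serious adverse events or the Health State Score as described, nor does it suit living arrangement and SGA as categories. The secondary aim on complications and the safety criterion are therefore left without a suitable stated analysis.

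The consequence is an effect estimate of undefined scale and an unsuitable error model, not a changed p-value. In the illustration, a 20-point risk difference could be reported as anything from 6.7 to 20 points. That range rests on assumed risks and on no events at entry; the mismatch between method and outcome rests on the text alone. The wording should be corrected, but the primary result does not depend on it.

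**What to change.** Limit the repeated-measures ANCOVA sentence to scales measured on at least two occasions, and add wording to this effect:

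*The proportion of participants with at least one complication, and the proportion with at least one serious adverse event, will be compared between blocks by risk difference with a score 95% interval, supported by a penalized logistic model adjusted for age, NIHSS and premorbid mRS. The Health State Score at 3 months will be compared by ANCOVA at that single time with the same covariates. Living arrangement and SGA will be compared by a method for categorical data.*

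This changes wording only and needs no new data, visits or participants. The cost is that a few simple models replace one, and adjusted estimates for rare events will be imprecise.

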## Discussion

Research has consistently shown that ASU care provides very limited opportunities for people with a stroke to be involved in physical activities and that patients are often alone. Increased activity levels after stroke are associated with better functional outcomes and reduced complication rates. In addition, with the aging population and the rising incidence in stroke, there is a strong need for the development of resource-efficient interventions that can improve patient and service outcomes without increasing staffing cost. The EE is an innovative interdisciplinary model of care that could build the capacity of acute stroke teams to deliver efficient and effective care for people with stroke.
